## Methods and analysis

### Study aims and objectives

The overarching aim of this research is to develop a robust, replicable identification system for digitally excluded older adults; and, working with community groups and those who are digitally excluded, refine and feasibility test an intervention (or interventions) to improve digital inclusion opportunities for those currently excluded.

Study objectives are to:

A. Identify those who are digitally excluded:

Survey methods will be used to estimate prevalence and predictors of digital exclusion in those aged 65+. Using this survey data, we will then use a predictive modelling approach that is implementable in primary care systems to systematically identify older people (aged 65+) at risk of digital exclusion or who are digitally excluded.Feasibility test our method of identifying those who are digitally excluded from primary healthcare registers.

B. Refine an intervention to meet their needs:

Identify the content, format and purpose of existing digital inclusion interventions through regional community consultation, and undertake a rapid review of the literature to understand the emerging evidence for digital training/support interventions for older people.Explore through interviews with a sample of older people the determinants and intersectional nature of digital exclusion.Undertake a series of co-production workshops—involving digitally included and excluded older people, and service providers—to identify and develop key components of an intervention(s) that would engage those who are currently digitally excluded (considering also how the intervention would be implemented in practice).

C. Feasibility test the intervention:

Provision of the newly-developed intervention to digitally excluded older people—to ascertain inclusion, feasibility, acceptability and inform intervention refinement (its content and how it is provided).

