##### Recruitment

A member of the clinical team at participating GP practices will identify eligible patients in their registers by running a prespecified search provided by the research team. Also included in the output of eligible patients will be a unique study ID, contact details, electronic Frailty Index (eFI) score (the eFI uses existing information held in electronic health records to measure frailty based on the accumulation of a range of deficits)^28^ and data items such as age, gender and postcode. These data will enable targeted telephone follow-up of non-responders to increase the representativeness of our sample.

GP practices will send via post to each eligible patient an introductory letter explaining what the study is about, followed 1 week later by: an invitation to participate, a participant information sheet (PIS), a survey and a ‘keeping in touch’ form on which participants can, optionally, provide their contact details if they wish to take part in later workstreams. They will also be sent a prepaid envelope for survey return directly to the research team. DocMail, a recognised secure method for contacting large numbers of patients for clinical purposes, will be used to minimise workload for GP practices, while retaining patient confidentiality. Those who do not wish to take part in the study will have a 2-week window following survey receipt to opt out from survey completion and any further study contact by returning the blank survey or telephoning the research team. Thereafter, we will augment our recruitment approach by a researcher based at each GP practice telephoning non-responders (an approach made clear in the PIS) to ask if they would be willing to complete the survey over the telephone. It will not be possible to follow-up all non-responders due to the volume of surveys sent, so the follow-up of participants will be prioritised using factors known to predict digital exclusion (eg, older age, female gender, socioeconomic deprivation derived from postcode, frailty).

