Surveys will also be distributed by researchers directly to older people at community groups, clinics, day centres and sheltered housing—those engaged during the earlier outreach work—as well as via other community contacts across our recruitment catchment area including areas with varying levels of deprivation. Researchers will offer to administer surveys directly with community group members who are in attendance when they visit, offering support with survey completion (eg, providing language support, or reading questions for those with visual impairment). Researchers might also visit participating GP practices and geriatric medicine outpatient clinics to invite attending patients to complete the survey.

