##### Data management and statistical analysis

GP practices will provide a list of study IDs with associated eFI scores to incorporate into the modelling work—an agreed approach enabling the research team to identify frailty status for survey respondents without obtaining any identifiable patient data. Index of Multiple Deprivation (IMD) will be derived from partial postcode (eg, AB99 1) entered by participants in the survey. We will compare demographic information of responders (eg, age, sex, eFI score) to that of the whole population of patients to whom surveys were sent. This whole population data will be obtained in summary form from the list of eligible participants generated at the practices.

A ‘hard’ definition of digital exclusion (ie,total non-use) will be used in the survey data analysis. Thus, participants will be defined as digitally included if they have independently (without help) performed one or more of the 22 online tasks specified in our survey, and digitally excluded if they have not performed any of these tasks. The tasks fall into four broad categories of online use: entertainment, healthcare, communication and buying things/managing money. However, we also wish to consider those who are narrow users and, as such, disadvantaged by not being able to fully engage with online activities.^10 18 26^ We will therefore also define participants as wide or narrow users, where wide users are those who perform one or more tasks in each of the four categories, and narrow users are those who do not perform at least one task in each category of use.

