Summary statistics will be produced to describe prevalence of digital exclusion and narrow use. Logistic regression will be performed with digital exclusion as the binary outcome, with candidate predictors of digital exclusion being age, gender, IMD, ethnicity, frailty category and lone living status. Using a ‘multilevel analysis of individual heterogeneity and discriminatory accuracy’ (MAIHDA) approach,^29^ participants will be assigned to strata based on categories of the above predictors. For example, a strata might be white women aged 65–75 with mild frailty, living alone in an area with high levels of socioeconomic deprivation. The variance will be compared between the model with and without the strata random effect, which indicates whether there are interaction effects (known as intersectionality) between the variables. Using the MAIHDA, precision weighted estimates of digital exclusion can be produced for each strata, with the raw predictions being further weighted towards the fixed effect estimates as the strata size gets smaller. Should there be no evidence of interactions, we will revert to a fixed effects logistic regression model which would enable us to include different functional forms of the included predictors (eg, age as a continuous rather than categorical predictor), and to consider including other predictors (such as memory and sight problems). As a sensitivity analysis, we will also refit the model with narrow/wide use as the binary outcome. If sensitivity analysis shows similar characteristics of those who are non-users and narrow users, both would be included in our definition of digitally excluded used in later workstreams.

Data will be coded and analysed using statistical software Stata. The model will be sense-checked with participants during the interviews and workshops in workstreams 4 and 5, respectively.

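### Prevalence is an objective, but its only stated analysis is summary statistics over a mixed-route sample, which describes no defined population; standardise it to the register totals already being collected

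*Protocol article*

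**What the plan says.** Under Study aims and objectives, the first objective reads: "Survey methods will be used to estimate prevalence and predictors of digital exclusion in those aged 65" (and over). Under workstream 1, Data management and statistical analysis, the prevalence analysis is one sentence: "Summary statistics will be produced to describe prevalence of digital exclusion and narrow use".

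Respondents reach the survey by three routes, described under workstream 1, Recruitment:

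- **Post.** Every eligible patient on the practice register is mailed.
- **Telephone.** Some non-responders are called. Not all can be reached, so "the follow-up of participants will be prioritised using factors known to predict digital exclusion". Older age, female gender, deprivation and frailty are given as examples. The stated purpose is: "These data will enable targeted telephone follow-up of non-responders to increase the representativeness of our sample".
- **In person.** "Surveys will also be distributed by researchers directly to older people at community groups, clinics, day centres and sheltered housing". Possibly also: "Researchers might also visit participating GP practices and geriatric medicine outpatient clinics to invite attending patients to complete the survey".

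Data on the mailed population are collected. The stated use is comparison: "We will compare demographic information of responders (eg, age, sex, eFI score) to that of the whole population of patients" to whom surveys were sent, and "This whole population data will be obtained in summary form from the list of eligible participants generated at the practices". The weighting mentioned in connection with the MAIHDA model is shrinkage of stratum estimates, not weighting to a population.

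**The concern.** A prevalence needs a population to refer to. The three routes have different selection probabilities. The telephone route selects on predictors of the outcome, and the in-person route has no known selection probability at all. Pooled summary statistics therefore depend on how many calls and visits were made as well as on how common exclusion is. The Sample size section adds that the other recruitment strategies will top up numbers if postal response is low, so the share from those routes would grow just when postal response is weakest.

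Selection on age, gender, deprivation and frailty does little harm to a regression that conditions on them. It does matter for a marginal quantity such as prevalence. At stake is whether the reported prevalence of exclusion and of narrow use can be read as a figure for the practice populations.

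**Working it through.** **Figures in the plan.** Sample size section: 0.15 × 6000 = 900 responses, which reproduces, with exclusion assumed at 31%. The 95% half-width is 1.96 × √(0.31 × 0.69 / 900) = 0.030, or 3.0 points.

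**Inputs the plan does not give (assumed here).** *h* is the share of the register in the high-priority group. *pH* and *pL* are the exclusion risks in that group and in the rest. *s* is the high-priority share of the sample. Then:

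crude − register value = (*s* − *h*)(*pH* − *pL*)

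**Step 1: both groups answer the post equally often.** Of 900 responses in total, *k* come from targeted calls, so *s* − *h* = (*k*/900)(1 − *h*).

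- Central case: *h* = 0.40, *pH* = 0.45, *pL* = 0.20, *k* = 300. Register value = 0.40 × 0.45 + 0.60 × 0.20 = 30%. Difference = (300/900) × 0.60 × 0.25 = +5.0 points.
- Smallest over *h* 30–50%, *pH* 40–50%, *pL* 20–25%, *k* 100–300: (100/900) × 0.50 × 0.15 = +0.8 points.
- Largest: (300/900) × 0.70 × 0.30 = +7.0 points.

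**Step 2: the high-priority group answers the post half as often.** Central inputs as above. Postal share = 0.5 × 0.40 / (0.5 × 0.40 + 0.60) = 0.25.

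| Responses from calls, of 900 | Sample share *s* | Difference (points) |
|---|---|---|
| 0 | 0.25 | −0.15 × 0.25 = −3.75 |
| 100 | (800 × 0.25 + 100)/900 = 0.333 | −1.7 |
| 200 | (700 × 0.25 + 200)/900 = 0.417 | +0.4 |
| 300 | (600 × 0.25 + 300)/900 = 0.50 | +2.5 |

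**Step 3: register value held at 31%, calls added on top of 900 postal responses.** Here *h* is 30% or 40%, *pH* is 45% or 55%, and *pL* is solved to give 31% overall.

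| Extra targeted responses | Crude, equal postal response | Crude, half postal response |
|---|---|---|
| 0 | 31.0% | 25.0–28.5% |
| 100 | 32.4–33.4% | 28.0–30.2% |
| 200 | 33.5–35.4% | 30.5–31.9% |
| 300 | 34.5–37.0% | 31.9–33.8% |

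The range is −6.0 to +6.0 points. To follow one population: with *h* = 0.40, *pH* = 0.55, *pL* = 0.15 and half postal response, no calls give 0.25 × 0.55 + 0.75 × 0.15 = 25.0%. With 300 extra responses the figure is (525 × 0.55 + 675 × 0.15)/1200 = 32.5%. Only the fieldwork differs.

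**Step 4: what standardising achieves.** Post-stratifying to the register shares returns 31.0% in every cell of step 3, because there response depends on the group alone. If excluded people respond at *q* times the rate of included people within each group, the observed risk becomes *qp*/(*qp* + 1 − *p*). With *h* = 0.40, *pH* = 0.45 and *pL* = 0.217, the post-stratified figure is 18.9% at *q* = 0.5, 24.3% at *q* = 0.7 and 36.5% at *q* = 1.3. That part of the bias stays.

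**The case against.** The strongest reply is that the targeting is a remedy. The calls go to non-responders to make the sample more representative, and people likely to be excluded may well answer the post less often. Step 2 bears this out: every targeted case there lies closer to the register value than the untargeted one, and all three fall within the 3.0-point half-width. This part of the reply stands. A reader might infer that a sample enriched for likely non-users must overstate prevalence. The documents do not support that inference, because it needs equal postal response in both groups, which is nowhere stated. Nor is enrichment shown for the in-person route: the Outreach work section includes informal groups whose members may be no more excluded than other patients.

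Three other strong readings also fail:

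- The text does not say the figure will be unweighted. It names summary statistics and is silent on weights, and a separate analysis plan could supply them.
- The Introduction's criticism of convenience sampling is aimed at work on barriers and facilitators. Earlier prevalence data are criticised for coming from national surveys that lack detail. The article does not contradict itself here.
- Prevalence is not the main output. The named key output is the model, and no later workstream is stated to use the prevalence figure.

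The reply does not supply a target population, or a rule that matches the number of calls to the response deficit. Without one of these, any cancelling of biases is a matter of chance. The document also goes beyond silence, since it names both the prevalence analysis and the use of the register data, and that use is comparison.

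**Conclusion.** The concern holds as a moderate point. Prevalence is an objective, and as described the estimate belongs to no defined population and moves with follow-up effort. Across the illustrative assumptions it lies between about 6 points below and 7 points above the register value, which can exceed the sampling half-width of about 3 points. These limits rest on assumed group sizes, risks, response ratios and numbers of calls, none of which the document gives, and the direction is undetermined. The register totals allow a partial correction only: they are summary data, exemplified by age, sex and frailty score, and cannot remove non-response that depends on exclusion itself. The regression and the identification model are largely unaffected, so this is an inexpensive improvement and the study does not turn on it.

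**What to change.** In workstream 1, Data management and statistical analysis:

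1. State that prevalence of exclusion and of narrow use refers to the register patients who were mailed.
2. Estimate it from ID-linked register respondents (post and telephone). Standardise to the register totals for age band, sex and frailty category by raking, post-stratification or averaging model predictions over register counts.
3. Add a deprivation margin. The register output already holds postcode; derive the index at the same partial-postcode level as in the survey, so that both sides match.
4. Report community- and clinic-recruited responses separately, and show the crude figure beside the standardised one.
5. State as a limitation that non-response related to exclusion within strata remains uncorrected.

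The cost is one more summary margin from the practices, a short analysis step, fewer responses in the prevalence estimate and usually a somewhat wider interval. As a guide, in the central case of step 1 the sample share is 0.60 against 0.40 on the register. The weights are 0.40/0.60 = 0.667 and 0.60/0.40 = 1.5, and the usual variance inflation for weighting is 0.60 × 0.667² + 0.40 × 1.5² = 1.17. The half-width then grows by about √1.17 = 1.08, from 3.0 to roughly 3.3 points.

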### Setting

Two general practitioner (GP) practices will be selected to take part in the first survey, and a further one to two practices in the second survey (workstreams 1 and 2). The number of practices selected to be determined by numbers of older people on practice registers and the required sample size. Primary care health registers provide the most inclusive population record available, so GP practices are the most suitable setting for survey distribution. We will work with practices that include some of the least and most socioeconomically disadvantaged populations in the UK, those with varying age profiles, and will ensure that our sample includes people from a range of minority ethnic backgrounds and from both urban and rural areas.

Scoping work with community service providers (workstream 3) will mostly take place remotely via telephone or video call, possibly with some visits to the organisations. Interviews with older people (workstream 4) will take place in participants’ homes or another community location of their choice. Co-production workshops (workstream 5) will be held in a community venue, accessible to participants. While we cannot specify the setting for the feasibility study to test the newly refined intervention (workstream 6) until it is developed, we expect it to be delivered in a suitable community venue. In all cases, participants will be given the option to engage with research activities over the telephone or a video platform if they have concerns about meeting a researcher or group face-to-face, or if they are unable to travel to a central venue.

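### The workstream 1 models have no GP practice term, so a between-practice difference that aligns with IMD or ethnicity enters those coefficients with understated standard errors; by how much depends on figures the protocol does not give

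*Protocol article*

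**What the plan says.** Under Setting, the protocol article states "Two general practitioner (GP) practices will be selected to take part in the first survey, and a further one to two practices in the second". It adds "The number of practices selected to be determined by numbers of older people on practice registers and the required sample size". The same section makes practice selection the route to a socioeconomic range: "We will work with practices that include some of the least and most socioeconomically disadvantaged populations in the UK". It also says the sample will cover several minority ethnic backgrounds and both urban and rural areas. Under Recruitment (workstream 1), every eligible patient on the registers is mailed, and researchers hand out further surveys through community groups, clinics, day centres and sheltered housing.

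Under Data management and statistical analysis (workstream 1), IMD comes from each respondent's partial postcode. The logistic model is specified as follows: "Logistic regression will be performed with digital exclusion as the binary outcome, with candidate predictors of digital exclusion being age, gender, IMD, ethnicity, frailty category". Whether the respondent lives alone completes the list. The MAIHDA step adds a random effect for strata built from those same variables: "The variance will be compared between the model with and without the strata random effect". If no interaction is found, a fixed-effects logistic model may take in further predictors; the examples given are memory and sight problems. No practice or recruitment-source term is named, and the Sample size section makes no allowance for clustering.

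The first objective is stated as "Survey methods will be used to estimate prevalence and predictors of digital exclusion in those aged 65" and over. The model is then applied in different practices in workstream 2, where calibration, discrimination and overall performance are assessed.

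**The concern.** Practice is the unit through which most respondents enter the sample. Two practices may differ in digital exclusion for reasons the model does not hold, such as local digital support, online access policy, outreach or rurality. If they also differ in deprivation or ethnic mix, the model cannot tell these influences apart, and it attributes the aligned part to IMD and ethnicity. Between two practices there is one contrast, yet the model's standard errors treat about 900 responses as independent.

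Two things are at stake. Predictors are a stated objective, so an IMD effect that is partly a two-practice difference could be reported as firmer than it is. The same coefficient is also carried into other practices in workstream 2. If two practices take part there, errors of opposite sign could cancel in pooled observed/expected and calibration-in-the-large.

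**Working it through.** **The plan's figure.** 15% × 6000 = 900 responses, as stated under Sample size. Split equally over two practices (an assumption), that is 450 each. The plan assumes 31% digitally excluded.

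**Inputs the protocol does not give.** These are the latent-scale practice ICC, taken as 0.01 to 0.10, and how unevenly high deprivation is spread over the practices. For the latter, a proportion p of one practice and 1 − p of the other live in high-deprivation areas, with p from 0.6 to 0.9.

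**Simulation.** Datasets of 2 × 450 respondents were generated with about 31–35% excluded, effects for age, gender, frailty and lone living, 25% v 5% minority ethnicity in the two practices, and no true IMD effect. The planned logistic model was fitted and IMD tested at a nominal 5%. There were 800 runs per cell. A second set of 1500 runs per cell supplied the 60/40 and 70/30 cells at ICC 0.01 and the cell at ICC 0.02, and repeated two of the 80/20 cells.

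**Hand check.**
- Practice variance: τ² = ICC/(1 − ICC) × π²/3.
- SD of the difference between two practice intercepts: √(2τ²).
- With equal practices, the share of that difference loading on a binary IMD indicator is 2p − 1.
- SD of the IMD coefficient ≈ √[(2p − 1)² × 2τ² + 0.153²], where 0.153 is the mean model standard error.
- Rejection rate ≈ 2 × [1 − Φ(1.96 × 0.153/SD)].

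At ICC 0.05 and p = 0.8: τ² = 0.173; √(2 × 0.173) = 0.588; 0.6 × 0.588 = 0.353; SD = √(0.353² + 0.153²) = 0.385; rejection about 44%. The simulated SD was 0.371, so the ratio to the model standard error is 0.371/0.153 = 2.4.

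At ICC 0.01 and p = 0.6: τ² = 0.0332; √(2 × 0.0332) = 0.258; 0.2 × 0.258 = 0.052; SD = √(0.052² + 0.153²) = 0.161; rejection about 6%. The simulated SD was 0.163.

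| ICC | Split | Hand check | Simulated, no practice term | Simulated, with practice indicator |
|---|---|---|---|---|
| 0.01 | 60/40 | 6.3% | 6.6% | – |
| 0.01 | 70/30 | 10.4% | 9% | – |
| 0.02 | 60/40 | 7.7% | 8% | – |
| 0.01 | 80/20 | 16.8% | 16–16.5% | 5.0% |
| 0.05 | 60/40 | 12.0% | 11.6% | 5.9% |
| 0.05 | 70/30 | 28.5% | 24.5% | 6.5% |
| 0.05 | 80/20 | 43.6% | 41–42.5% | 4.4% |
| 0.05 | 90/10 | 54.5% | 51.5% | 5.2% |
| 0.10 | 80/20 | 57.5% | 56.9% | 5.2% |

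**Second parameterisation.** A separate simulation (1000 runs per cell, IMD log-odds ratio 0.3) varied the share of IMD variance lying between practices. In the binary set-up that share is (2p − 1)²: 4% at 60/40 and 36% at 80/20. The ratio of true SD to model standard error, with 95% interval coverage, was:
- ICC 0.01: 1.13 (93%) at a 10% share, 1.26 (88%) at 25%, 1.58 (79%) at 50%.
- ICC 0.05: 1.56 (79%) at a 10% share, 2.16 (64%) at 25%, 2.97 (49%) at 50%.

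With a fixed practice indicator, coverage was 94–97% in all cells.

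**MAIHDA.** Simulating the stratum-variance test at the 80/20 split showed no inflation from the omitted practice effect.

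**The case against.** The strongest reply is that the size rests on two inputs the protocol does not supply, and that the model is built for prediction. Several parts of it stand.

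- A reader might infer that the two practices are picked to contrast, one deprived and one affluent. The Setting section says only that practices include some of the least and most disadvantaged populations, which also fits practices that are each mixed.
- A reader might infer that the whole practice difference is credited to deprivation. IMD and ethnicity are recorded per respondent, and community recruitment adds variation, so only the aligned part is absorbed.
- A reader might conclude that the standard errors are far too small. With a low ICC and modest imbalance the understatement is small.
- A reader might extend the point to the MAIHDA test for interactions. The check gave no support for that.
- No Wald test of IMD is announced. Transfer to other practices is examined in workstream 2, which is where a poorly transferring coefficient could show.
- A fixed practice indicator cannot be carried to new practices, and it uses the parameter allowance. Under an assumed shrinkage criterion (target 0.9, Cox-Snell R² 0.1), going from 11 to 12 parameters raises the required sample from 934 to 1019. This argues against making it the primary prediction model.
- The article is condensed, and an unseen analysis plan may already contain a site check.

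What does not fall is the specification itself. The article lists its predictors and its one random effect, practice is in neither, and predictors of digital exclusion are an objective in their own right. With one or two validation practices, pooled calibration alone is limited evidence of transfer.

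**Conclusion.** The point holds in a conditional form. With respondents drawn mainly from two practices and no practice term, any between-practice difference aligned with IMD or ethnicity enters those coefficients and their model standard errors are too small. The size cannot be fixed from the protocol. It runs from negligible (about 7% rejection at a nominal 5%, ICC 0.01, 60/40 split) to large (about 41–43%, standard error understated about 2.4-fold, ICC 0.05, 80/20 split), and further still at more extreme assumed values. These figures assume two equal practices, a null IMD effect and normally distributed practice intercepts. They do not bear on the MAIHDA stratum-variance comparison. They also do not show that the planned prediction model should be replaced.

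**What to change.** Keep the planned models for prediction and make two additions.

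1. In Data management and statistical analysis (workstream 1), prespecify a sensitivity analysis that refits the logistic model with a fixed practice indicator and a separate level for community-recruited respondents who cannot be linked to a practice. Report the IMD and ethnicity coefficients with and without the indicator, and describe them as firm predictors only if they persist within practice. A random practice effect or cluster-robust standard errors are not usable with two practices.
2. In Data management and analysis (workstream 2), report observed/expected and calibration-in-the-large by practice as well as pooled when two practices take part.

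No new data are needed: practices supply the study ID lists, so practice is known for mailed respondents. Some community recruits may be patients of the two practices, which is why the extra level is limited to those who cannot be linked.

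The cost is one or two extra parameters in the sensitivity model and a wider IMD interval there (standard error up about 3% at a 60/40 split, 24% at 80/20, 64% at 90/10). The adjusted coefficient also loses any effect of deprivation that acts at practice level, so both versions should be shown.
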